#### Traditional care pathway

There was no detailed plan in the controlled group, and anti-infection, anti-coagulation, and other measures were taken to prevent complications during the perioperative period.

### Randomization and allocation

After the screening, patients will be randomized into two groups with an allocation ratio of 1:1. The randomization will be generated via SAS PROC PLAN software (SAS Inc., Cary, NC, USA) by an independent third-party clinical research organization (Institute of Basic Research in Clinical Medicine, China Academy of Chinese Medical Science) and concealed from the researchers by a senior data manager who is not involved in the study. The group assignment list will be sealed in opaque envelopes and be opened by the researchers following informed consent procedures and baseline testing.

### Blinding

All the investigators, physicians, nurses, assessors, analysts, and participants will be blinded to the group assignment until the end of the trial, when all statistical analyses are finished. If, after the first administration, any adverse event potentially related to the treatment occurs, the study physician will re-evaluate the participant, and PI will decide whether the non-blinded procedure is necessary. If non-blinding is required, the allocation information will be provided.

### Outcome measurements

#### Primary outcome measurement

LOS (length of stay) associated with ITF is a major public health issue due to the aging population, and it is the most objective outcome of evaluating the recovery pathway. Furthermore, high LOS would correspond with increases in postoperative complications [14, 19]. So we choose the LOS at discharge as the primary outcome measurement to assess the speed of recovery. Economic indicators including major medical expenses, bed expenses, drug expenses, inspection expenses, operation expenses, cost of anesthesia, nursing care, and blood transfusion are the other primary outcome measurement.

#### Secondary outcome measurements

Postoperative joint-specific function will be measured using the Harris score, which is widely used to assess the joint function of life for ITF patients. The Harris score is composed of 10 questions, 2 questions (ROM and absence of deformity) for the physician physical examination component and 8 questions for the patient-reported outcome component [20–24]. VAS is a reliable and valid measurement of pain. It has a horizontal, 100-mm-long line, with “no pain” recorded on the left side (score 0) and “pain as bad as it could be” on the right side (score 10) [25]. The other secondary outcomes included time to get out of bed, 30-day readmission rates, postoperative transfusion rates, discharge to home, and mortality.

### Safety assessments

Infection, deep venous thrombosis, and cardiovascular accidents will be recorded at each visit during treatment.

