**Methods/design:**

We will conduct a prospective randomized, blinded, controlled trial to compare the effectiveness of ERAS care pathway with traditional care pathway and to investigate whether the ERAS care pathway can improve the perioperative outcome in ITF patients undergoing intramedullary fixation. A total of 60 patients with ITF will be enrolled and treated with the two care pathway, respectively. Length of stay, economic indicators, Harris score, VAS score, time to get out of bed, 30-day readmission rates, postoperative transfusion rates, discharge to home, and mortality will be evaluated. Any signs of acute adverse reactions will be recorded at each visit during treatment.

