## Introduction

With the aging of society, the incidence of intertrochanteric fracture (ITF) is increasing. It is easy to bring bedsore, urinary tract infection, lung infection, and other complications. Intertrochanteric fracture has become a major public health issue with a high mortality rate for old patients and increased the economic burden [1, 2]. Currently, ITF is treated with both surgical and non-surgical methods. Surgical treatment has great advantages in alleviating pain, restoring hip function, improving quality of life, and avoiding complications such as deep vein thrombosis and cardiovascular accident caused by long-term bed rest, so surgical treatment is the first choice of treatment [3–6]. Currently, PFNA (proximal femoral nail anti-rotation, PFNA) is a mature surgical treatment for senile ITF, which is characterized by maintaining strong fixation, biomechanical stability, and minimal invasion [7, 8].

ERAS (Enhanced Recovery after Surgery) is one of the two important development directions leading the development of modern surgery in the twenty-first century, which is first proposed by Kehlet in 1997 [9]. ERAS aims to integrate the perioperative diagnosis and treatment concept by optimizing a series of effective approaches and methods with evidence-based medical evidence, so as to reduce trauma invasion and alleviate the stress reaction caused by surgery. The core of the ERAS is a powerful guarantee for patients to accelerate their recovery after surgery [10–13]. At present, ERAS has been applied in the treatment of many orthopedic diseases including artificial joint replacement [14].

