### Patient population and recruitment procedure

Participants will be recruited from Longhua Hospital affiliated to Shanghai University of Traditional Chinese Medicine. Prospective participants will be interviewed by the coordinators and informed of the eligibility criteria and the procedure. Those who are eligible and willing to participate in the study will be screened initially by baseline assessment and then diagnosed based upon clinical manifestations, physical examination, and imaging. Participants will be informed that participating in the trial was absolutely voluntary and withdrawal from the trial can be made at any time. In case of withdrawal, the data collected will not be deleted and will be used in the final analyses. A data compilation form including all variables of interest and all potential risks will be completed by the corresponding research center. The information obtained will be stored in an electronic database for subsequent statistical analysis. Recruitment will start in January 2020 and is expected to end in July 2021. The final follow-up of all participants will be completed on 30 September 2021. The overview of the participant processing and the schedule of evaluation is provided in Fig. 1.

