To our best knowledge, our study is the first elaborately designed, randomized, controlled trial to evaluate the clinical effect of the ERAS project integrated Chinese and western medicine on perioperative outcomes in ITF patients undergoing PFNA. A hallmark of ERAS is coordination between care services before and after surgery and continual evaluation of postoperative course with attention toward pain control, functional recovery, and patient satisfaction to improve standards of care. So the study is designed as a comprehensive study of LOS, economic indicators, pain relief, functional outcome, and complications. Outcome measurements are widely used in research to establish baselines, evaluate the effect of an intervention, and motivate patients’ self-evaluation. LOS was the most commonly assessed metric in comparative analyses. And a comparative reduction in LOS was reported in most studies using the ERAS protocol. Improved cost-effectiveness of surgical interventions is also a primary objective when implementing strategies for faster recovery in this study. The calculation of cost-effectiveness provided is based on data provided by our Department of Finance. The study is also to evaluate whether ERAS program can lead to a reduction in hospitalization costs, care costs, and nursing costs, which supports the cost-effectiveness of “fast-track” protocols in PFNA surgery. The VAS measurements, which have been found valid, reliable, and easy to apply in researches, are often used as the criterion standard to evaluate the pain intensity. The Harris score, a self-administered questionnaire, has been widely adopted as the criterion standard to estimate disease activity for its reliability and validity. Another aim of the study lies in reducing both intra- and postoperative adverse events and complication, which have the potential to impair the patients’ perioperative well-being and to prolong recovery. Especially in elderly patients, or in those with severe comorbidities, strict patient selection is key to both eligibility for safe ERAS and treatment in specialized short-stay clinics that may not have an ICU available. Administration of prophylactic medication against infections and thrombosis, prevention of hypothermia, and fluid imbalance, as well as operative measures, has therefore become integral to successful implementation of ERAS [27–30].

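### The abstract and the safety section disagree on which adverse events are recorded; if the safety section's three-item list governs, some harms have no stated place in the record

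*Protocol article*

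**What the plan says.** The protocol article gives two rules for safety recording.

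- Safety assessments, the only section devoted to safety: "Infection, deep venous thrombosis, and cardiovascular accidents will be recorded at each visit during treatment".
- Abstract, Methods/design: "Any signs of acute adverse reactions will be recorded at each visit during treatment".

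Three other places touch on harms.

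- Blinding, on possible unblinding: if "any adverse event potentially related to the treatment occurs, the study physician will re-evaluate the participant".
- Patient population and recruitment procedure: "A data compilation form including all variables of interest and all potential risks will be completed by the corresponding research center".
- Secondary outcome measurements: "The other secondary outcomes included time to get out of bed, 30-day readmission rates, postoperative transfusion rates, discharge to home, and mortality".

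The Discussion sets a broad goal: "Another aim of the study lies in reducing both intra- and postoperative adverse events and complication". It closes by hoping that the trial will inform on the safety as well as the efficacy of ERAS. Statistical analyses plans a safety analysis by intention to treat.

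**The concern.** Both recording rules apply to visits during treatment, yet their scope differs. A site that works from the methods section is told about three event types and has no instruction to write down anything else. A site that works from the abstract records whatever it sees.

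This matters because of what is being tested. Table 1 writes into the ERAS pathway an anti-inflammatory analgesic, sedative-hypnotic or anti-anxiety drugs, a three-day analgesia pump, dexamethasone, tranexamic acid, a systolic pressure target, acupuncture, manipulation and oral Chinese medicine, with erythropoietin for one type of anaemia. All patients are over 75. Several plausible harms of these components lie outside infection, deep venous thrombosis and cardiovascular accident.

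Events that nobody was asked to record may not be recoverable later. A safety table with three rows would then stand behind a general statement about adverse events.

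**Working it through.** The article states no figure on this point, so the check is mainly a comparison of texts.

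**Step 1. Does any text set up a general adverse event record?**

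| Place | Scope | General record? |
|---|---|---|
| Abstract, Methods/design | Any sign of an acute adverse reaction | Yes, but only in the abstract |
| Safety assessments | Three named event types | No |
| Blinding | Any possibly related adverse event | No: prompts re-evaluation and a decision on unblinding; recording and analysis are not mentioned |
| Patient population and recruitment procedure | A form covering potential risks | Unclear: the risks are not defined |
| Secondary outcome measurements | Transfusion, 30-day readmission, mortality | No: specific endpoints only |

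The open rule therefore appears once, in the abstract, and the dedicated section does not repeat it.

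**Step 2. If the safety section governs, where would each kind of harm be found?**

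- Infectious, thrombotic and cardiovascular events: in the three-item list, whether ERAS prevents or causes them.
- Bleeding: partly, through postoperative transfusion.
- Any harm that ends in readmission within 30 days or in death: through those outcomes, in both arms.
- Renal or hepatic injury, hypotension short of a cardiovascular accident, sedation-related events, and reactions to acupuncture, manipulation or herbal medicine that lead to none of these: no stated place.
- Bedsores: no stated place, although the Introduction says of the fracture that "It is easy to bring bedsore, urinary tract infection, lung infection, and other complications". The urinary and lung infections in that sentence already fall under infection.

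**Step 3. Would detection be equal in the two arms?** Table 1 asks for monitoring of blood counts and of liver, kidney and cardiac function under ERAS. The Traditional care pathway section describes no detailed plan and no such monitoring. Without common questions in both arms, detection of the same event may differ by arm.

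**Step 4. How likely is an unlisted harm to occur at all?** The event rates here are assumptions; the article gives none. The arm size of 36 comes from Sample size calculation (72 in total). The abstract gives 60 in total, so 30 per arm is shown as well. The formula is P(at least one) = 1 − (1 − p)^n.

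| Assumed true rate p | n = 36 | n = 30 |
|---|---|---|
| 2% | 1 − 0.98^36 = 0.52 | 1 − 0.98^30 = 0.45 |
| 5% | 1 − 0.95^36 = 0.84 | 1 − 0.95^30 = 0.79 |
| 10% | 1 − 0.90^36 = 0.98 | 1 − 0.90^30 = 0.96 |

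A moderately common unlisted harm would thus probably occur. Even with complete recording, zero events in 36 patients leaves a one-sided 95% upper bound of 1 − 0.05^(1/36) = 0.080, or 8.0%. A blank that arises because nobody was asked says less still. These figures give the chance of occurrence. They do not measure a difference between arms.

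**The case against.** The safety section does not say that only these three events are recorded. It can be read together with the abstract as general recording plus three named events. The unbinding of possible related events under Blinding and the form under recruitment also point to wider capture, and an article commonly leaves adverse event forms to the full protocol. This weakens any claim that harms will certainly be lost. It does not remove the disagreement, because the article states both rules and leaves the reader to guess which one sites follow.

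A reader might infer more: that harms of treatments given only in the ERAS arm go uncounted, so that ERAS will look safer than it is. The article does not support this.

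- Control care is left undefined, so control patients may receive some of the same drugs. The components are specified only for ERAS, which is not the same as given only there.
- The list and the secondary outcomes catch some harms that ERAS could cause.
- The same list applies to both arms. A bias towards ERAS needs unlisted harms to be more frequent under ERAS.
- Some omissions could work the other way. Table 1 stresses early exercise and turning, so uncounted bedsores might hide a benefit of ERAS. Anticoagulation is named for control but not in Table 1, so unrecorded bleeding need not favour ERAS. Laboratory monitoring stated only for ERAS could raise detection in that arm.

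The Discussion also remarks that "strict patient selection is key to both eligibility for safe ERAS", while the exclusion criteria name no comorbidity. That is a matter of eligibility and adds nothing to the point on recording.

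**Conclusion.** The point holds in a limited form. The abstract and the safety section conflict on the scope of adverse event recording and must be reconciled. On the condition that the safety section governs, harms of components in the ERAS pathway that fall outside its three categories, and that do not lead to transfusion, readmission or death, have no stated place in the record. Three categories cannot carry the Discussion's general aims on adverse events and safety.

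The gap could favour ERAS, but only if the unlisted harms are more frequent in that arm. Neither the direction nor the size of any such bias can be derived from the article. The probabilities of 0.52, 0.84 and 0.98 rest on assumed rates of 2%, 5% and 10% in 36 patients, and show only that such events would be likely to occur. The change should be made, since it is cheap and missing events may not be recoverable.

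**What to change.** Rewrite Safety assessments so that it adopts the abstract's open rule, worded as all adverse events:

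- Record every adverse event in both arms, with the same form and the same questions at every visit.
- Keep infection, deep venous thrombosis and cardiovascular accidents as events of special interest, and add bedsores.

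This takes about a sentence in the protocol and an open adverse event page in the case report form. It needs no new visits and alters no treatment. The downside is slightly more data entry.

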### Statistical analyses

Prior to all analyses, a detailed statistical analysis protocol will be developed. All data will be analyzed in the clinical research center of Longhua Hospital affiliated to Shanghai University of TCM by statisticians blinded to allocation using the SPSS 20.0 statistical software (SPSS Inc., Chicago, IL). Efficacy and safety analyses will be conducted according to the intention-to-treat principle using the “last observation carried forward” rule. Before randomization, baseline characteristics will be collected as descriptive statistics for each patient, including gender, age, BMI, duration of symptoms, preoperative red blood cell count, and preoperative hemoglobin count. The data analysis of the primary outcome is based on the per-protocol population as a supportive analysis. Mean, standard deviation, median, quartiles and inter-quartiles for continuous variables, and frequency for categorical variables will be calculated. Continuous variable followed the normal distribution will be presented as means with standard deviations (SDs) and calculated by an independent sample Student’s *t* test; otherwise, the data will be expressed as medians with ranges, and non-parametric tests will be used. Categorical variables will be expressed as number (%) and analyzed by *χ*^2^ test or Fisher’s exact test. A *P* value of less than 0.05 is defined as statistically significant with two-sided 90% confidence intervals (CIs). Missing data will be input with the last observed response carried forward for all measures using the “last value carried forward” principle.

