## Materials and methods

### Study design

This study is a prospective, outcome assessor- and data analyst-blinded, randomized controlled design study that compared an ERAS care pathway cohort with standardized care pathway cohort. Emergency admissions with a primary diagnosis of ITF between January 2020 and July 2021 in our hospital will be selectively enrolled. All patients will receive their operation at our hospital where elective surgeries take place predominantly, and they will be treated with PFNA intramedullary fixation at our institution.

The objective of this proposed study is to investigate whether ERAS care pathway will lead to perioperative improvement in ITF patients undergoing intramedullary fixation. The principal investigator (PI) is responsible for the overall project and organizing Steering Committee meetings. PIs of sub-center departments are responsible for gathering experts to carry out the project. An independent Steering Committee will be responsible for affairs such as participants’ safety, meetings, recruitment and follow-up of participants, and quality control. The coordinating center is responsible for communicating protocol modifications and providing materials. This trial includes a 2-week treatment period and a 3-month follow-up period. Outcome assessments will be conducted at baseline, as well as at 3, 14, 30, and 90 days (Fig. 1).

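### Harris and VAS are to be compared by unadjusted two-group tests although outcomes are scheduled at baseline; adjusting for the baseline score may gain precision and costs almost nothing

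*Protocol article*

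**What the plan says.** The Study design section sets the timing for outcomes in general: "Outcome assessments will be conducted at baseline, as well as at 3, 14, 30, and 90 days". It gives no schedule by instrument, and the figure that carries the schedule is not shown in the text at hand.

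Under Secondary outcome measurements, "Postoperative joint-specific function will be measured using the Harris score", and the VAS is introduced as the pain measure: "VAS is a reliable and valid measurement of pain".

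The Statistical analyses section has a single rule for continuous variables. Those that are normally distributed "will be presented as means with standard deviations (SDs) and calculated by an independent sample" comparison, namely the t test. For variables judged non-normal, the article says instead that "the data will be expressed as medians with ranges, and non-parametric tests will be used". It names no covariate, no analysis of covariance (ANCOVA), no repeated-measures model and no analysis visit. It also does not say whether the tested quantity is the score at a visit or the change from baseline. The same section lists baseline characteristics, "including gender, age, BMI, duration of symptoms, preoperative red blood cell count, and preoperative hemoglobin count", and announces a fuller plan: "Prior to all analyses, a detailed statistical analysis protocol will be developed".

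**The concern.** If a scale is scored before treatment and again at four later visits, a plain two-group test of a later score makes no use of where each patient started. The arms are small (36 each), and the section on randomisation and allocation describes no stratification, so some chance difference in baseline pain or function is likely. Part of that difference would remain in an unadjusted estimate.

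Harris and VAS are the direct measures of function and pain, and the Discussion lists pain relief and functional outcome among the things the study is meant to assess. They help to show whether a shorter stay comes with preserved function and pain control. What is at stake is the precision of these two secondary comparisons, not their validity.

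**Working it through.** **The plan's own figure.** The article states no power, effect size, standard deviation (SD) or baseline correlation for Harris or VAS, so there is nothing to reproduce for them. The sample size of 72 (36 per group) was derived for length of stay. It cannot be reproduced from the stated inputs, because a formula for rates is applied to means in days and no SD is given. Below, 36 per arm is simply taken as the stated size.

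**Inputs.**
- 36 per arm and two-sided alpha 0.05 (Sample size calculation).
- 29 per arm as a second case: 36 × (1 − 0.20) = 28.8, using the stated 20% dropout.
- Assumed: a true difference that gives the unadjusted test 80% power at 36 per arm.
- Assumed: correlation rho between baseline and later score, varied from 0 to 0.7, with equal variances at the two times.

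**Formulas** (normal approximation).
- Standardised difference: d = (1.960 + 0.842) × √(2/36) = 0.66.
- ANCOVA leaves a fraction 1 − rho² of the variance, so power = Φ(d × √(n/2) / √(1 − rho²) − 1.960).
- A t test on change has variance 2(1 − rho) relative to the raw score, so √(2(1 − rho)) replaces √(1 − rho²).

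**Example**, rho = 0.3, n = 36: 2.802 / √0.91 = 2.937; 2.937 − 1.960 = 0.977; Φ(0.977) = 83.6%.

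| rho | Variance left, 1 − rho² | ANCOVA, 36/arm (raw-score t: 80%) | t test on change, 36/arm | ANCOVA, 29/arm (raw-score t: 71.0%) |
|---|---|---|---|---|
| 0 | 1.00 | 80.0% | 50.8% | 71.0% |
| 0.1 | 0.99 | 80.4% | 55.1% | 71.5% |
| 0.2 | 0.96 | 81.6% | 60.1% | 72.8% |
| 0.3 | 0.91 | 83.6% | 65.8% | 75.0% |
| 0.4 | 0.84 | 86.4% | 72.5% | 78.3% |
| 0.5 | 0.75 | 89.9% | 80.0% | 82.7% |
| 0.7 | 0.51 | 97.5% | 95.1% | 94.1% |

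**Check with the non-central t**, charging ANCOVA one degree of freedom. The standardised difference for 80% is then 0.670, and adjusted power is 81.6, 83.6, 86.3 and 89.9% at rho 0.2, 0.3, 0.4 and 0.5. At rho = 0 it stays at 80.0%, so the lost degree of freedom does not show at this rounding. From a 90% starting point (difference 0.775) the figures are 91.1, 92.5, 94.2 and 96.3%.

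**Change score against ANCOVA.** The ratio of their variances is (1 − rho²) / [2(1 − rho)] = (1 + rho)/2, which never exceeds 1. Apart from the one degree of freedom, ANCOVA is at least as precise whatever rho is. The change score falls below the raw-score test whenever rho is under 0.5.

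**Carry-over of imbalance.** In a raw-score comparison, a chance baseline difference of 1 SD unit shifts the expected later difference by about rho units: about a fifth at rho 0.2 and half at rho 0.5.

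**The case against.** **This belongs to the analysis plan.** Model form and covariates for secondary scales are often left to the plan, and the article announces one. That would settle the matter if the article were silent. But it names a test for every continuous variable, and a plan that followed it would keep the less efficient choice. The point addresses that stated choice, not a gap.

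**A valid test is not an error.** This stands. Randomisation protects the unadjusted comparison, and the absence of stratification on Harris or VAS is no defect. The point is about efficiency on secondary outcomes.

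**Harris and VAS may not be scored at baseline.** A reader might infer that they certainly are. The article speaks of outcome assessments in general, describes Harris as postoperative function, and names neither scale among the baseline characteristics. Against that, the list is introduced as non-exhaustive, the envelopes are opened after baseline testing, and most other outcomes (stay, costs, transfusion, discharge to home, readmission, mortality) have no baseline value. Baseline scoring is the natural reading, but it remains an inference.

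**Baseline may not be ignored.** A reader might also infer that it is. The text does not exclude a t test on change. That reading does not rescue the plan, since it gives 65.8% against 83.6% for ANCOVA at rho 0.3.

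**The gain may be small.** The patients are "Emergency admissions with a primary diagnosis of ITF between January 2020 and July 2021". A Harris score taken just after a fracture may sit near its floor, and the VAS may reflect acute fracture pain; either may predict later scores weakly. That is a judgement, not a documented figure, but it is reasonable, and it limits the size of the benefit.

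**Conclusion.** The point holds as a modest improvement. The only analyses named for Harris and VAS are unadjusted two-group tests, and a baseline-adjusted comparison would be at least about as precise at negligible cost. With 36 per arm and 80% unadjusted power, the gain is under 2 points at rho up to 0.2, about 4 points at 0.3 and about 10 points at 0.5. With 29 per arm and the same true difference, 71.0% rises to 72.8, 75.0 and 82.7% at rho 0.2, 0.3 and 0.5.

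These sizes rest on an assumed effect and an assumed correlation, and on both scales being scored at baseline. The documents do not support the stronger claim that power is definitely lost on function and pain, because no correlation is given and it may be weak. Nor does a chance baseline difference pass in full into the estimated effect; it does so only in proportion to rho.

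**What to change.** State by instrument whether Harris and VAS are scored at baseline. Where they are, replace the generic rule for these two outcomes with this: the between-arm comparison at each post-baseline visit is the mean difference adjusted for the patient's own baseline score, reported with its confidence interval. Either ANCOVA at each visit or a repeated-measures model with arm, visit, arm by visit, baseline and baseline by visit would serve. Keep the unadjusted or rank-based test as a sensitivity analysis if residuals are clearly non-normal; this preserves a role for the non-parametric branch already in the text.

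The cost is a wording change and about one degree of freedom per model, with negligible loss if baseline proves uninformative. No visits or patients are added, and no data if the scales are scored at baseline as the schedule suggests. If the repeated-measures form is chosen, the sentences on carrying the last value forward must be made consistent with it.

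### A normality check decides whether the primary cost outcome is compared by means or by ranks, and the likely rank branch does not address mean cost, which the stated aim needs

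*Protocol article*

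**What the plan says.** Primary outcome measurement names two primary outcomes. The first is LOS: "So we choose the LOS at discharge as the primary outcome measurement to assess the speed of recovery". The second is a set of costs: "Economic indicators including major medical expenses, bed expenses, drug expenses", followed by further expense items.

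Statistical analyses gives one rule for continuous variables, with no exception for the primary outcomes. The normal branch reads "Continuous variable followed the normal distribution will be presented as means with standard deviations (SDs) and calculated by an independent sample Student’s" t test. The other branch reads "otherwise, the data will be expressed as medians with ranges, and non-parametric tests will be used".

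The same section adds three things that bear on this point:

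- Descriptive statistics are not conditional on normality: "Mean, standard deviation, median, quartiles and inter-quartiles for continuous variables, and frequency for categorical variables will be calculated".
- A P "value of less than 0.05 is defined as statistically significant with two-sided 90% confidence intervals (CIs"). The quantity that these intervals describe is not stated.
- A detailed statistical analysis protocol is to be written before any analysis.

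The Discussion gives the purpose of the cost outcome. Better cost-effectiveness is called a primary objective, and the study is to evaluate "whether ERAS program can lead to a reduction in hospitalization costs, care costs, and nursing costs".

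**The concern.** The observed data choose what is compared. If cost passes the check, the arms are compared on mean cost. If it fails, they are compared by a non-parametric test, in practice presumably a rank test, and described by medians.

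These are different questions. A hospital or payer that asks whether a pathway saves money needs the mean, because mean cost times the number of patients is the total bill. A cost-effectiveness statement rests on the same quantity. A rank test asks whether a patient in one arm tends to cost more than a patient in the other. If the pathway changes the spread of cost, the two answers can part company:

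- A pathway that only makes spending more uniform can be declared different in cost when the mean has not moved.
- A real saving that comes from fewer very expensive stays can be missed, because the typical patient costs the same.

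The second case matters to the sponsor. A pathway with detailed components is compared with a control arm that has no detailed plan, so a narrower spread under ERAS (Enhanced Recovery after Surgery) is conceivable. The article gives no data on it.

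**Working it through.** **Inputs from the protocol article.** The t-test/non-parametric rule and the 5% two-sided level (Statistical analyses); 36 patients per group (Sample size calculation). The Abstract gives 60 in total, so 30 per group is shown where available. The article states no figure for this point that could be reproduced.

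**Assumptions.** Log-normal cost; normality judged by Shapiro-Wilk at 5% in each arm; Student t test if both arms pass, otherwise Mann-Whitney; 3,000 to 4,000 simulated trials per setting. The article gives no cost distribution, normality criterion or named rank test, so results are shown over a range of coefficients of variation (CV).

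**Step 1. How often does the rule switch to ranks?** (same CV in both arms)

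| CV | 36 per arm | 30 per arm |
|---|---|---|
| 0.3 | 65% | 58% |
| 0.5 | 95% | 88% |
| 0.75 | 99.7% | 99% |
| 1.0 | 100% | 99.9% |

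**Step 2. Why ranks and means can disagree.** For log-normal cost, median = mean / √(1 + CV²). With mean 1 in both arms:

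- CV 0.3: 1/√1.09 = 0.958
- CV 0.4: 1/√1.16 = 0.928
- CV 0.6: 1/√1.36 = 0.857
- CV 0.8: 1/√1.64 = 0.781

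So at equal mean cost, CVs of 0.3 v 0.6 put the medians 11% apart (0.857/0.958 = 0.895). CVs of 0.3 v 0.4 put them only 3% apart (0.928/0.958 = 0.969). The more variable arm looks cheaper.

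**Step 3. Equal mean cost, 36 per arm: how often is a difference declared at 5%?**

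| CVs | Protocol's rule | Welch test of means |
|---|---|---|
| equal | 4.6% to 5.0% | about 5% |
| 0.5 v 0.6 | 6.3% | 4.6% |
| 0.4 v 0.5 | 6.1% | 4.8% |
| 0.3 v 0.4 | 6.5% | 4.6% |
| 0.4 v 0.6 | 11% | 5% |
| 0.3 v 0.6 | 17% | 5.5% |
| 0.3 v 0.8 | 34% | 6.8% |

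The Monte Carlo standard error near 5% is √(0.05 × 0.95/4000) = 0.3 percentage points, and below 1 point at 34%.

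**Step 4. The reverse error: equal median cost, different mean cost, 36 per arm.**

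| SDs of log cost | Ratio of mean costs | Protocol's rule | Welch |
|---|---|---|---|
| 0.3 v 0.6 | 1.14 | 6% | 13% |
| 0.4 v 0.8 | 1.27 | 5% | 17% |
| 0.3 v 0.8 | 1.32 | 7% | 25% |
| 0.4 v 1.0 | 1.52 | 6% | 29% |

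Here mean costs truly differ by 14% to 52%, yet the rule rejects at little more than its nominal level.

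**Step 5. A proportional saving with equal spread (CV 0.5).** A 20% saving is detected in 51% of trials by the rule and 48% by Welch; a 30% saving in 87% and 85%. In this setting the choice hardly matters.

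**Step 6. LOS.** With identical distributions (mean 9.2 days, assumed SD 4) the rule keeps a 5.0% error rate. At the article's 5.8 v 9.2 days, the rule and Welch disagree on significance in 0.6% of trials with an assumed SD of 3 and 6% with an SD of 4, and the rule has at least 99% power. At an assumed smaller effect, 7.5 v 9.2 days with SD 3, the mean and rank tests disagree in about 12% of trials, and the rank test has more power (73% v 65%).

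**The case against.** Four points can be made for the plan.

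**A later analysis plan is promised.** The normality criterion, the name of the rank test and the quantity behind the interval are details that an article may leave to it, and their absence is not the fault here. The switch itself, however, is stated, applies to a primary outcome, and would carry over unless it is changed.

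**The simulated harm depends on the scenario.** This stands. The large figures need equal means and a CV that doubles or more. With modest differences in spread the rule rejects in 6% to 6.5% of trials, and with equal spread in about 5%. Nothing in the article says which case applies.

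**The article does not say mean cost.** It speaks of a reduction in costs. But it also names cost-effectiveness as a primary objective, and that is a statement about average or total cost. A comparison of ranks cannot support it.

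**Summaries are planned anyway.** A reader might infer that the plan gives no estimate of money or days saved. The text does not support that: arm means and SDs are to be calculated whatever the distribution, and confidence intervals are mentioned. What is missing is narrower: no between-group difference is named for those intervals to describe.

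A reader might also extend the criticism to LOS with equal force. Step 6 does not support that. The error rate is sound, the rank test can be the more powerful one, and at the article's own effect size the two tests rarely disagree.

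**Conclusion.** The point holds for the economic primary outcome. The stated rule will probably judge cost by ranks and medians, which do not answer whether mean or total cost falls. The fault is a mismatch between test and question, not a general inflation of false positives: when both arms have the same distribution the rule holds its level.

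The size is conditional. At equal mean cost the rule declares a difference in about 6% of trials at CVs of 0.3 v 0.4, rising to 34% at 0.3 v 0.8, against 5% to 7% for Welch. With equal medians it largely misses mean differences of 14% to 52%. All of this rests on log-normal cost, Shapiro-Wilk as the check and Mann-Whitney as the fallback, none of which the article gives.

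For LOS, only a lesser point remains: the test is not fixed in advance, and no difference in days is named as the estimate.

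**What to change.** **Cost.** Remove the normality switch. Always compare arithmetic means (Welch or bootstrap) and report the difference in mean cost with a 95% CI, which also matches the 5% test. Keep the rank test as a sensitivity analysis and medians as description.

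**LOS.** Name one test now, either a comparison of means or the rank test. Whichever is chosen, report the difference in mean days with a 95% CI beside it.

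**Cost of the change.** Wording only: no extra patients, visits or data. The statistical downside is that a comparison of means can lose some power against ranks when data are skewed. For cost with a proportional saving at CV 0.5 the loss was 2 to 3 percentage points (48% v 51%, 85% v 87%). For LOS in the 7.5 v 9.2 day example it was 8 points (65% v 73%), which is a fair reason to name the rank test for LOS.
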